#### Deidentification methods.

De-identification involves two steps. The first is the removal of direct identifiers. The second is taking one or both of the following additional steps: 1) the removal or alteration of other information that could potentially be used to re-identify an individual, and/or 2) the use of controls and safeguards in the data access environment to prevent re-identification [25]. The study data will be de-identified using the following methods:

Direct identifiers, such as names, addresses, will be removed as soon as the data integrity is verified and cleaned and prior to analysis, and never reported publicly.Indirect identifiers, such as dates of birth, zip codes, and medical codes, will be removed as soon as the data integrity is verified and cleaned and prior to analysis, and never reported publicly.Removal of the direct and indirect identifiers will be done as early as possible in the data cleaning phase to safeguard the data in case of re-identification.When presented or published, data will *always be aggregated and grouped* so that identification is not possible. We will suppress cells/rows or information with 5 or less persons and avoid reporting outliers in ranges (e.g., such as persons aged 107 years of age, or a death in a 2-month-old).

#### Public release model.

The public release modelled data occurs after extensive cleaning and analysis. The released data is aggregated for descriptive analyses. The focus of the analysis is mathematical models that provide only group-wide estimates.

### Statistical methods

We will summarise safety and efficacy data using descriptive statistics, including means, medians, and frequencies. We will use statistical tests to compare groups (e.g., chi-square tests for categorical data, t-tests for continuous data). We will also adjust for multiple comparisons to control for type I error.

Logistic regression models will be used to assess accuracy in the presence of potential confounders. This includes sex (female/male), age (by age group), person collecting sample (self-collect/clinician collect), comorbidities, symptomatology (symptomatic/asymptomatic), duration of symptoms, and whether blood was present in the sample. Subgroup analysis will be conducted according to disease type (e.g., viral, or bacterial).

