## Abstract

Obtaining a stool specimen for diagnostic testing of enteric conditions (e.g., gastroenteritis) can be a challenging and unpleasant experience. A person is required to obtain a sample pot from a healthcare location, return home and wait until they have a bowel motion, and then deal with the challenges of returning the sample to the clinic or pathology centre. This trial aims to identify whether the simpler approach of obtaining a rectal swab is effective for diagnosing enteric conditions. Recruitment will take place in a variety of settings, including suspected norovirus clusters, Hepatitis A clusters, in both hospital, and community settings. We will compare paired stool and rectal swab sample polymerase chain reaction (PCR) testing to determine whether rectal swabs are a reliable proxy for faecal sampling. Persons who would normally be provided with a faecal specimen container, will also be provided with a rectal swab for self-collection or clinician-collection (within 24 hours of the bulk faeces collection). We will assess the sensitivity, specificity, positive predictive value, negative predictive value using standard confusion matrix. The gold standard reference will be considered the bulk faeces PCR tests. We hypothesise that rectal swab PCR testing will be equally as effective as bulk faeces PCR testing. If successful, rectal swab PCR testing could be implemented as routine practice with several key benefits. Firstly, it would improve the patient experience by conveniently enabling stool collection at the point of care, which is rarely possible currently. Secondly, it would reduce healthcare costs, and streamline collection processes by eliminating the need for persons to return to a clinic to deliver specimen. Thirdly, the ease of testing will likely increase testing rates and compliance, leading to better diagnoses and more accurate clinical care. The protocol described has the potential to revolutionise daily clinical practice.

**Trial registration**: Australian New Zealand Clinical Trials Registry (ANZCTR): ACTRN12624000095561.

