## Methods

This is a single group paired sampling prospective trial comparing the diagnostic accuracy between an established method and an alternative method of diagnosis. Participants of the study are required to use both sampling methods to allow for comparison of results. A broad timeline of the trial is presented in Fig 1. This trial was registered with the Australian New Zealand Clinical Trials Registry (ANZCTR) (registration number: ACTRN12624000095561) on 02/02/2024. Ethics approval was granted for this trial by the Metro North Human Research Ethics Committee (HREC) (EC00168) on 19/12/2023. Written or verbal consent to participate will be obtained from each participant. Records of consent will be stored securely.

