#### Primary outcomes.

We will assess the sensitivity, specificity, positive and negative predictive value, and positive and negative agreement value, using 2x2 tables. The gold standard will be bulk faeces PCR testing. Sensitivity is the proportion of individuals with the disease who test positive with rectal swabs. We will assess the cycle threshold (CT) values using general linear models if the relationship is linear as expected and estimate the receiver operating curves and areas under the curve to assess for the potential to need differential CT value cutoffs. All results will be reported using 95% confidence intervals.

The R statistical suite will be used for all analyses and data visualisation. All estimates will be presented with 95% confidence intervals (CI). P-values <0.05 are deemed significant, and p-values <0.1 are considered trends.

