#### Secondary outcomes.

We will calculate the number and percentage of participants experiencing at least one adverse event, and the total number of adverse events reported. We will tabulate the distribution of adverse events by severity (mild, moderate, severe) for both the rectal swab and bulk faeces groups. Summarise AEs by expectedness (expected, unexpected) and relatedness (definitely, probably, possibly, unrelated) for each group. We will report the incidence rates of adverse events per 100 participant-days for each group, allowing for comparison over different follow-up periods. We will use chi-square tests or Fisher’s exact tests to compare the incidence rates of adverse events between the rectal swab and bulk faeces groups. We will use ordinal logistic regression to analyse the severity of adverse events, treating severity as an ordinal outcome. We will include group (rectal swab vs. bulk faeces) as the main predictor and adjust for potential confounders (e.g., age, gender, mode of testing, and location of testing).

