#### Objectives of interim analysis.

Recruitment Rates: Assess the rate of recruitment and discuss the barriers and facilitators to successful participant recruitment.Safety Monitoring: Ensure participant safety by identifying any significant adverse events early. Review adverse event reports, including severity, relatedness, and unexpected events. Analyse differences in safety profiles between the rectal swab and bulk faeces groups.Efficacy Assessment: Non-inferiority assessments will be performed to monitor for inferiority of rectal swab PCR in comparison with traditional bulk faeces testing. Evaluate the primary endpoint of difference of accuracy of specimen collection methods, the rate of pathogen detection.Trial Continuation Decision: Provide data to support decisions on continuing, modifying, or stopping the trial.Compliance and Protocol Adherence: Assess the adherence to study protocols, including the proper collection and handling of specimens.

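### Adverse events in the same participants are to be compared with tests for independent groups, and the general methods sentence leaves room for the same error in detection and CT values

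*Protocol article*

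**What the plan says.** The Methods section of the protocol article describes one group of people: "This is a single group paired sampling prospective trial comparing the diagnostic accuracy between an established method and an alternative method of diagnosis". It adds: "Participants of the study are required to use both sampling methods to allow for comparison of results".

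The Secondary outcomes section then treats the two samples as two groups. Chi-square or Fisher's exact tests are to "compare the incidence rates of adverse events between the rectal swab and bulk faeces groups". For severity it plans an ordinal logistic regression: "We will include group (rectal swab vs. bulk faeces) as the main predictor". The adjustments given as examples are age, gender, mode of testing and location of testing. No term identifies the participant.

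The interim objectives use the same language: "Analyse differences in safety profiles between the rectal swab and bulk faeces groups".

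The Statistical methods section opens with descriptive summaries of safety and efficacy data and continues: "We will use statistical tests to compare groups (e.g., chi-square tests for categorical data, t-tests for continuous data"). It does not say which groups are meant, or whether the t-test is paired.

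The primary analysis is set out separately, as sensitivity, specificity, predictive values and "positive and negative agreement value, using 2x2 tables", with bulk faeces PCR as the reference and 95% confidence intervals throughout.

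The article names no McNemar test, paired t-test, paired interval, or mixed or conditional model.

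**The concern.** Chi-square, Fisher's exact and unpaired t-tests assume that the two sets of observations come from different people. Here they come from the same person, usually close together in time. If someone who reports a problem with one collection is more likely to report one with the other, or someone positive on one sample is more likely to be positive on the other, the two results are positively correlated. A test for independent groups ignores this, and its standard error for the difference is too large.

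For adverse events, an excess from the swab could then go unflagged. That matters because the comparison is a stated secondary outcome and feeds the interim safety review. If the general sentence were also applied to swab-versus-bulk detection, a real shortfall in the swab's positivity could go unflagged too. The Abstract's hypothesis is that the two methods are equally effective, so an insensitive comparative test would lean towards it.

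**Working it through.** The plan gives no figure for this comparison, so there is none to reproduce. The check has two parts.

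**1. Which test is assigned to which data**

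| Section | Comparison | Method named | Same people on both sides? |
|---|---|---|---|
| Secondary outcomes | Adverse events, swab vs bulk | Chi-square or Fisher's exact | Yes, stated |
| Secondary outcomes | Severity, swab vs bulk | Ordinal logistic model, no participant-level term listed | Yes, stated |
| Statistical methods | Undefined groups | Chi-square, t-tests (as examples) | Not stated |
| Primary outcomes | Swab against bulk reference | 2x2 tables with 95% intervals | Yes, and the table uses the pairing |

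**2. What ignoring the pairing does**

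The article gives no adverse event rates, so detection serves as the illustration. Positivity of about 25% and sample sizes below 600 are in the Sample size calculation section. The discordant counts are assumed: 300 pairs, 75 bulk-positive, 8 of these missed by the swab, 1 swab-only positive. Swab-positive is therefore 75 − 8 + 1 = 68.

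- Difference: (8 − 1)/300 = 0.0233.
- Unpaired standard error: √[0.25×0.75/300 + 0.2267×0.7733/300] = 0.0348.
- Paired standard error: √[(8 + 1) − (8 − 1)²/300]/300 = √8.837/300 = 0.0099.
- Ratio: 0.0348/0.0099 ≈ 3.5.
- Unpaired 95% interval: 0.0233 ± 1.96×0.0348 = −0.045 to 0.091. Paired: 0.0233 ± 1.96×0.0099 = 0.004 to 0.043.
- Pearson chi-square without correction, 75/300 vs 68/300: χ² = 0.45, p = 0.50.
- Exact McNemar, 8 vs 1: 2×[C(9,0) + C(9,1)]/2⁹ = 20/512 = 0.039.

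The gap comes from the covariance. The two variances differ by 2×cov/n, where cov = 67/300 − 0.25×0.2267 = 0.167.

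Simulation under assumed swab sensitivity of 80% and specificity of 99%, with 25% positivity and two-sided 0.05: at 300 pairs, chi-square rejects in about 4% of trials and exact McNemar in 86 to 88%. At 600 pairs the figures are about 30% and over 99%. When the two positivity rates are truly equal, chi-square rejected in 0.0% of runs at 100, 300 and 600 pairs, against a nominal 5%.

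The loss depends on the size of the deficit and the sample. With no swab-only positives and 25% positivity, chi-square detects a sensitivity of 70% in 74% of runs at 300 pairs and 99.8% at 600, and a sensitivity of 80% in 62% at 600.

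For adverse events the same variance formula applies, but neither the rates nor the correlation are known. With positive correlation the unpaired test is too conservative; with none it is about right; with negative correlation it would reject too often.

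**The case against.** The strongest reply is that the general sentence is only illustrative. It does not say that its groups are swab and bulk, and the paragraph after it lists truly independent participant groups (sex, age group, self- versus clinician-collected, symptomatic or not), for which chi-square and t-tests are correct. A condensed article may also leave the choice of test to an analysis plan. This stands for the Statistical methods section, where the fault is conditional on how the sentence is applied. It does not answer the Secondary outcomes section, which names the tests and the two groups outright. That is a test assigned to the wrong kind of data, not a detail left out.

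Three stronger inferences are tempting, and the documents support none of them.

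- A reader might infer that a clearly inferior swab would usually look no different in the main result. The primary estimates do not rest on a two-group test. In the example above, sensitivity would be reported as 67/75 = 89.3% (exact 95% interval 80.1 to 95.3%), whatever chi-square gives.
- A reader might infer that p>0.05 will be taken as proof of equal effectiveness. No section says so; inferiority is monitored through margins on the difference in accuracy.
- A reader might want the paired difference in overall positivity judged against the final 0.10 margin. That would not protect against a poor swab: the example's difference of 2.3 points (0.4 to 4.3) lies well inside it, because missed positives are diluted by the bulk-negative majority.

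**Conclusion.** The point holds in a limited form. In the Secondary outcomes section, tests and a model suited to independent groups are assigned to two observations on each participant. In the Statistical methods section, the wording allows the same error for detection and CT values but does not commit to it.

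Where the error applies and within-person correlation is positive, it can turn a detectable difference into an unremarkable one: p=0.50 against p=0.039 in the example, with a standard error about 3.5 times too large. That figure rests on assumed discordant counts and on detection data, which are likely to be more strongly correlated than adverse events. The size for adverse events is unknown, and its direction depends on the sign of the correlation.

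The primary sensitivity, specificity and agreement estimates with their 95% intervals are not affected. The change should still be made, because an analysis plan that follows the article would inherit the error.

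**What to change.** **Secondary outcomes section.** Replace chi-square or Fisher's exact for swab versus bulk with McNemar's test on participants with an event after one collection only, or with a paired difference in proportions and its 95% interval. Add a participant-level term to the ordinal severity model (mixed model or GEE), and say which, since they estimate different odds ratios.

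**Statistical methods section.** Define the groups. State that any swab-versus-bulk comparison of detection uses exact McNemar with a paired difference and 95% interval, and any comparison of CT values uses a paired t-test or a mixed model. Keep chi-square and unpaired t-tests for independent participant subgroups, such as self- versus clinician-collected.

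**Objectives of interim analysis.** Apply the same paired methods to the comparison of safety profiles.

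**Cost.** Wording and standard R functions; no extra participants or samples. One practical condition: a paired adverse event analysis needs each event recorded against the collection it followed. The structured question in the Follow-up section asks about the swab only, so the call script would need a matching question for bulk faeces if that comparison is kept.

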### Sample size calculation

A sample size analysis with a wide range of input parameters, as described by Hajian-Tilaki 2014, demonstrates that less than 600 samples will be sufficient to cover a range of diseases (Fig 2) [16]. Assuming that 30% of samples will contain an organism (“proportion positive”) with an expected sensitivity of at least 95% (“sensitivity priors”) means we will require a sample size of no more than 61 paired samples. As the prevalence of disease in samples decreases, the sample size required is higher. For a sensitivity of 95% and a prevalence of 20%, the sample size increases from 61 to 92. These estimates are based on general sensitivity assumptions and a simplified disease prevalence model, with the literature reporting non-specific prevalence to be approximately 25%, and sensitivity estimates typically >90% [17–20]. These estimates may change slightly as recruitment progresses and the distribution of pathogens becomes clearer. To address potential variability across different pathogens, stratified analyses will be conducted. Power calculations for key pathogen subgroups indicate that, for a sensitivity of 95% (with a range of 90–99%), a minimum of 73 positive samples is required per pathogen subgroup.

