#### Minimum data requirements.

At a minimum, data collected for each participant should include:

Identifiers (name, address, date of birth, contact details, comorbidities)Recruitment details (date of recruitment, date of consent, proof of consent, date that test packs were posted, symptomatology, duration of symptoms, presence of blood in faeces (if applicable))Sample collection details (where samples were collected (e.g., at home), who collected the sample (e.g., self-collect), date and time each sample was collected, date samples were submitted to pathology lab)Bulk faeces and rectal swab test results (date that lab testing was conducted for each sample, presence of visible faeces for the rectal swab only, positive/negative detection results for each sample)Follow-up information (date of follow-up attempts, which sample was collected first as reported by the participant, rough estimate of time difference between samples collected, adverse event details, preferred sample method)

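### The seven-covariate logistic model of accuracy is too large for the few swab errors the protocol implies, and its outcome may mix misses with false positives

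*Protocol article*

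**What the plan says.** Under Statistical methods the article fixes the method and names the outcome: "Logistic regression models will be used to assess accuracy in the presence of potential confounders". It then lists the covariates: "This includes sex (female/male), age (by age group), person collecting sample (self-collect/clinician collect"), followed by "comorbidities, symptomatology (symptomatic/asymptomatic), duration of symptoms, and whether blood was present in the sample". Subgroup analysis by disease type, such as viral or bacterial, is added in the same paragraph. The outcome variable, the set of pairs analysed, the covariate coding and the estimation method are not described further.

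Outcomes lists accuracy as a measure of its own beside sensitivity and specificity. The Primary outcomes part of the statistical section takes sensitivity and specificity from 2×2 tables against bulk faeces PCR.

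Sample size calculation plans only for the precision of sensitivity. It states that "less than 600 samples will be sufficient to cover a range of diseases", begins from "Assuming that 30% of samples will contain an organism" with sensitivity of at least 95%, and adds: "For a sensitivity of 95% and a prevalence of 20%, the sample size increases from 61 to 92". It also cites a literature prevalence of about 25%, literature sensitivities typically above 90%, and 73 positives per pathogen subgroup. Timeline expects 3–6 swabs a week, with recruitment completed within two years.

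**The concern.** In a logistic model the information is limited by the rarer outcome, here the pairs in which the swab is wrong. A test expected to be 95% sensitive produces few such pairs, and seven or more coefficients have to be estimated from them. With so few events, ordinary maximum likelihood often has no finite solution (separation), and where it has one the intervals are very wide.

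The second problem is the outcome. If accuracy means correct versus incorrect classification over all pairs, misses among bulk-positive pairs and false positives among bulk-negative pairs become the same event. Unless the two error rates are equal, any factor that shifts the share of positives shifts the error rate, although it does nothing to the swab's performance.

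At stake is the adjusted evidence on what modifies swab performance, including whether self-collected swabs do as well as clinician-collected ones.

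**Working it through.** **Inputs from the protocol article.** Sensitivity 95% (literature above 90%), positives 20–30%, total below 600, and 73 positives per pathogen subgroup (Sample size calculation). Accrual of 3–6 a week over 104 weeks is 312–624 pairs (Timeline). **Assumed:** specificity, which the article does not give, is taken as 95–99%.

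**Reproducing the plan's own figures.** Positives needed = 1.96² × Se × (1 − Se) / d², where d is the half-width of the 95% interval. The article does not state d, so it is inferred.
- d = 0.10: 3.8416 × 0.95 × 0.05 / 0.01 = 18.25 positives. 18.25/0.30 gives 61 pairs and 18.25/0.20 gives 92.
- d = 0.05: 72.99, which gives 73 positives.

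All three stated numbers are reproduced. None of them sizes a multivariable model: 61 pairs at 30% positive imply 61 × 0.30 × 0.05 = 0.9 misses.

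**Parameters.** Sex 1, age group at least 1, collector 1, comorbidities at least 1, symptomatic 1, duration at least 1, blood 1. That is at least 7 slopes, or 8 parameters with the intercept.

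**Reading A: events are missed positives among bulk-positive pairs.** Misses = N × prevalence × (1 − Se).

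| N | Positive | Se | Misses | Per slope (÷7) |
|---|---|---|---|---|
| 312 | 25% | 95% | 3.9 | 0.56 |
| 600 | 25% | 95% | 7.5 | 1.07 |
| 600 | 30% | 95% | 9.0 | 1.29 |
| 624 | 30% | 95% | 9.4 | 1.34 |
| 600 | 20% | 90% | 12 | 1.7 |
| 600 | 30% | 90% | 18 | 2.6 |

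A pathogen subgroup with 73 positives gives 73 × 0.05 = 3.65 misses, or 0.52 per slope.

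**Reading B: events are all discordant pairs.** For N = 600, 25% positive and Se 95%, there are 7.5 misses plus 450 × (1 − Sp) false positives.
- Sp 99%: 7.5 + 4.5 = 12 (1.7 per slope)
- Sp 98%: 7.5 + 9 = 16.5 (2.4 per slope)
- Sp 95%: 7.5 + 22.5 = 30 (4.3 per slope)

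**Effect of pooling.** Error rate = p(1 − Se) + (1 − p)(1 − Sp). With Se 95% and Sp 99%, p = 20% gives 0.010 + 0.008 = 1.8%, and p = 30% gives 0.015 + 0.007 = 2.2%. The error rate differs by a factor of 1.22 with swab performance unchanged. With Se and Sp both at 95% the effect vanishes.

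**Stability.** This was checked by simulation: 300 data sets per case, one slope per covariate, no true effects. The covariate distributions are assumptions: sex and age group 50% each, clinician or self-collect split 40/60, comorbidity 30%, symptomatic 80%, blood 10%, and duration set to zero without symptoms. The last column is exp(1.96 × median standard error) for the collector odds ratio in runs that converged.

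| Case | Mean events | No finite fit | 95% limits, fold either way |
|---|---|---|---|
| 73 positives, Se 95% | 3.6 | 91% | 8.2 |
| 150 positives, Se 95% | 7.3 | 65% | 4.6 |
| 180 positives, Se 95% | 9.1 | 49% | 4.1 |
| 150 positives, Se 90% | 15.2 | 27% | 3.2 |
| 180 positives, Se 90% | 17.9 | 22% | 2.9 |
| 600 pairs, pooled, Sp 99% | 11.9 | 44% | 3.3 |
| 600 pairs, pooled, Sp 98% | 16.9 | 24% | 2.8 |
| 600 pairs, pooled, Sp 95% | 29.7 | 5% | 2.2 |

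The separation rates depend on the assumed covariate mix. With blood in 10% of samples, the chance that none of 9 misses has blood is 0.9⁹ = 0.39, which alone explains much of the 49%. The width of the collector interval depends less on that choice.

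**The case against.** The strongest reply is that the article names models, in the plural, without saying that all covariates enter one model, without defining the outcome and without ruling out penalised or reduced fits. Separate models by bulk status would fit the wording, and an analysis plan may settle these details. This stands in part. Pooling is a natural reading of the separate listing of accuracy, but it is not stated. What the article does fix is the method and a seven-item adjustment list, and that list is long for the expected events on either reading.

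Four stronger conclusions a reader might draw are not supported:

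- **That one model both pools the two error types and has only 4–9 events.** The 4–9 are the events only when bulk-positive pairs are analysed alone, and then nothing is pooled. A pooled model has more events.
- **That the model cannot give usable estimates.** At 90% sensitivity there may be 12–18 misses. With 30 discordant pairs, separation was rare (5%). Recruiting people with a high pre-test probability, which the article allows, would also add positives.
- **That symptom duration breaks the model because asymptomatic people have none.** Asymptomatic people can enrol, but a nested term handles this. It is a coding detail, and a value that does not apply need not be imputed.
- **That visible faeces, collection order and interval were wrongly left out.** The article records them (for example "presence of visible faeces for the rectal swab only" under Minimum data requirements), but a list introduced as what the adjustment includes need not be exhaustive.

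Nor is adjustment itself misplaced. Patient factors cannot confound swab against bulk faeces within a pair, but they can confound self- against clinician-collection, which is not randomised.

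**Conclusion.** The concern holds as a mismatch between the size of the model and the expected number of errors, together with an outcome that is not pinned down. On the protocol's planning figures a model of missed positives has about 4–9 events for at least seven slopes (12–18 for 600 pairs if sensitivity is 90%). A pooled accuracy model of 600 pairs at 25% positive has about 12–30 if specificity is 99–95%, and it then also confuses positivity with performance whenever the two error rates differ. A full ordinary maximum-likelihood fit is unlikely to be stable, and within a pathogen subgroup of 73 positives (about 4 misses) it would usually fail.

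This rests on the article's sensitivity, prevalence and accrual figures, on an assumed specificity, and on all listed covariates entering together. The primary sensitivity, specificity and predictive values come from 2×2 tables and do not depend on this model.

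**What to change.** Replace the single outcome of accuracy with two models: swab positive among bulk-positive pairs (sensitivity) and swab negative among bulk-negative pairs (specificity). Fit each by Firth-penalised or exact logistic regression with a short pre-specified list: collector (self or clinician) plus one or two patient factors, such as symptomatic status, that may confound the collector comparison.

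Do not adjust the collector effect for visible faeces on the swab. It may lie on the path from who collects to whether the organism is detected, so adjusting could remove part of the effect of interest. Report it and the remaining listed factors as stratified sensitivity and specificity with exact limits. If duration is used, nest it within symptomatic participants. Within viral and bacterial subgroups, give stratified estimates rather than refitting the full model.

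The cost is wording only, with no new data. The price is fewer mutually adjusted estimates. Penalisation does not create information: with 3.9 misses, two or three terms still leave about 2.0 or 1.3 events per term (3.9/2 and 3.9/3), so wide intervals should be expected and reported as such.
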